## Abstract

The KOSovan Acute Coronary Syndrome (KOS-ACS) Registry is established as a prospective, continuous, nationwide, web-based registry that is operated online. The KOS-ACS registry is designed with the following objectives: (1) to obtain data on the demographic, clinical, and laboratory characteristics of ACS patients treated in Kosovo; (2) to create a national database with information on health care in ACS patients treated in Kosovo; (3) to identify the national features of associations between ACS characteristics and clinical outcomes, including mortality, complications, the length of hospital stay, and the quality of clinical care; and (4) to propose a practical guide for improving the quality and efficiency of ACS treatment in Kosovo. The Kosovo Society of Cardiology and University of Prishtina will be responsible for the development of the KOS-ACS registry and centralized data analysis at the national level. The KOS-ACS Registry will enroll all patients admitted, at any of the registered clinical centers, with the diagnosis of ACS and who will be clinically managed at any of the Kosovo hospitals. Data on patient demographics, clinical characteristics, previous and hospital drug treatment, and reperfusion therapy will be collected. The type of ACS (unstable angina, NSTEMI, or STEMI) will also be clearly defined. The time from first medical contact to balloon inflation (FMC-to-balloon) and door-to-ballon time will be registered. In-hospital death and complications will be registered. Data on the post-hospital primary outcome (MACE: cardiac death, all-cause mortality, hospitalization, stroke, need for coronary revascularization) of patients, at 30 days and 1 year, will be included in the registry.

## 1. Introduction

Acute coronary syndrome (ACS), which includes unstable angina, non-ST segment elevation myocardial infarction (NSTEMI), and ST segment elevation myocardial infarction (STEMI), is a common manifestation of atherosclerotic cardiovascular disease (CVD), and its recognition has a direct impact on patients’ morbidity and mortality [1,2,3,4,5]. Numerous national registries, worldwide, do exist, and many include patients with ACS [6,7,8,9,10,11,12,13,14,15]. The main goal of these registries is to fill the gap between real-world data, on the treatment of patients with ACS, and current relevant clinical guidelines, derived from randomized controlled trials [16,17]. Other important objectives of ACS registries are to investigate the clinical characteristics of patients with ACS in different countries/regions. Thus, the most important rationale of ACS registries is evaluating and optimizing national ACS practice strategies in light of the available up-to-date strong international evidence. This rationale has been useful in many countries [18,19,20,21,22,23,24,25,26], having identified wide geographic variations in the management of patients with STEMI, especially in receiving timely primary PCI [27]. 

Kosovo is the youngest European country and does not have any prospective designed registry for ACS. Some observational single-center data in different time periods have shown that the treatment of patients with ACS in Kosovo [28,29,30] did not strictly comply with current clinical guidelines, resulting in significantly sub-optimum clinical outcomes. Therefore, the Board of Kosovo Society of Cardiology, in its role to rectify such a situation, has approved establishing a National ACS Registry. The results of such a registry are expected to have an important impact on health care providers of the country, persuading them to take adequate measures for improving the clinical care of patients with ACS. This National Registry is described as the KOSovan Acute Coronary Syndrome (KOS-ACS) Registry. 

The aim of this article is to discuss the objectives and design of the KOS-ACS Registry which should also be of interest to other nations. 

## 2. Description of KOS-ACS Registry 

### 2.1. Objectives

The KOS-ACS registry is designed with the following objectives: (1) to obtain data on the demographic, clinical, and laboratory characteristics of ACS patients treated in Kosovo; (2) to create a national database with information on health care in ACS patients treated in Kosovo; (3) to identify the national features of associations between ACS characteristics and clinical outcomes, including mortality, complications, the length of hospital stay, and the quality of clinical care; and (4) to propose a practical guide for improving the quality and efficiency of ACS treatment in Kosovo (Figure 1). 

### 2.2. Desing of the KOS-ACS Registry 

The KOS-ACS Registry is established as a prospective, continuous, nationwide, web-based registry that is operated online (www.kosacs.com, access on 1 June 2024). The design of the KOS-ACS Registry is based on the current clinical guidelines’ points on the diagnosis and treatment of ACS [31]. 

Only members of the registry, who will have username, a unique identification number, and password, will have access to the registry. The menus of the webpage are designed to minimize the number of keyboard errors. Several technical measures are introduced to maximize the accuracy of data. The web interface of the KOS-ACS contains these forms with the following titles: (1) personal data of ACS patients; (2) history of present event of ACS; (3) past relevant history; (4) risk factors for CVD; (5) results of physical examination; (6) results of echocardiography; (7) results of laboratory tests; (8) details of intervention, if happened; (9) prior therapy; (10) details of medical treatment of ACS; (11) recommendations at discharge; and (12) complications and clinical outcomes. 

### 2.3. The Developers of the KOS-ACS Registry 

The Kosovo Society of Cardiology and University of Prishtina will be responsible for the development of the KOS-ACS Registry and centralized data analysis at the national level. The KOS-ACS was established in November 2023 by researchers and cardiologists, members of the Kosovo Society of Cardiology, with the support of information technology specialists. It will start collecting data for ACS on 1 June 2024. 

### 2.4. Participation 

Participation in the KOS-ACS is voluntary and free-of-charge. Any clinical center that provides health care for ACS patients, both in the private and public health care system in Kosovo, is entitled to participate in the KOS-ACS Registry by sending a request to the technical support team of the KOS-ACS. In December 2023, all centers were invited to take part in the KOS-ACS by the Kosovo Society of Cardiology, and all agreed to participate. The registry will have one principal investigator and ten coordinators (one per each center).

### 2.5. Patients 

The KOS-ACS Registry will enroll all patients admitted, at any of the registered clinical centers, with the diagnosis of ACS according to conventional European Guidelines [31] and who will be clinically managed at any of the Kosovo hospitals including the University Clinical Centre of Kosova in Prishtina, six Regional Hospitals in six Kosovo districts, and three private hospitals (Supplementary Data). The enrollment of patients is planned to start in May 2024 and to continue for at least two years, with potential extension (Figure 2). Inclusion criteria comprise the following: (1) any type of ACS (unstable angina, NSTEMI, or STEMI) as a presumptive diagnosis and (2) patients age ≥ 18 years, irrespective of gender. The exclusion criteria will be (1) symptoms considered as ACS at admission which were not consistent with acute cardiac ischemia and (2) patients with ACS accompanied by a significant comorbidity, such as any trauma, traffic accident, or severe gastrointestinal bleed/operation or procedure directly before admission (Figure 1). 

### 2.6. Data Elements

The key data elements and definitions of the KOS-ACS Registry database were developed using the 2023 ESC Guidelines for the management of ACS [31] and the ACVC-EAPCI EORP STEMI Registry of the ESC [32].

Data on patient demographics, clinical characteristics, previous and hospital drug treatment, and reperfusion therapy will be collected. All conventional and new risk factors will also be part of the questionnaire (Supplementary Data) patients will be requested to fill out. The type of ACS (unstable angina, NSTEMI, or STEMI) will also be clearly defined. The time from first medical contact to balloon inflation (FMC-to-balloon) and door-to-ballon time will be registered. In-hospital death and complications will be registered. Data on the post-hospital primary outcome (MACE: cardiac death, all-cause mortality, hospitalization, stroke, need for coronary revascularization) of patients, at 30 days and 1 year, will be included in the registry (Figure 3). 

### 2.7. Data Collection

All centers participating in the KOS-ACS Registry will be asked to include all patient’s inclusion/exclusion criteria for ACS based on the recent ESC Guideline for ACS [31] or future eventual guidelines delivered by ESC. The source of patient data will be hospital charts for admitted patients with ACS in all centers. A detailed user manual will be developed, to help participants in the registry, and will be available on the KOS-ACS Registry website. 

In each participating center, at least one physician will be trained to log patient data into the registry. The content of data-entry web forms will be simple and user friendly. Every 3 months, experts from the KOS-ACS Registry will check the validity of entered data by reconciling randomly selected records with the data of patients’ hospital charts. 

### 2.8. Data Security 

Database and web security issues are important for registries. The KOS-ACS website has been designed in a way that allows all users to be assigned with a unique username/password combination which is mandatory to log on to the KOS-ACS Registry. All transactions will be recorded automatically in the web server’s log. All data entered on the website will be protected by a password on a safe server of the KOS-ACS Registry. Subject identification will be possible only at the local study site, and participating centers will be able to review and modify patient data. ACS patients’ data added to the KOS-ACS Registry may be updated but cannot be removed. The entered data will be stored on the central database on the central server at KOS-ACS Registry. These measures are undertaken to ensure the confidentiality and security of the data. 

### 2.9. Ethical Aspects 

The study protocol of the KOS-ACS Registry, including patient information and consent forms has been reviewed and approved by the Ethics Commission of the Kosovo Doctors Chamber and by the Ethics Committee of the University of Prishtina. All patients must give informed consent before entering their personal and clinical data in the KOS-ACS Registry. The standard informed consent form will be available on the KOS-ACS Registry website, in order to allow the local coordinator to obtain consent. Patients will give informed consent after transfer from an intensive care unit (ICU) to a cardiac/coronary care unit. In the case of death in the ICU, consent to use the patient’s data anonymously will be given by a patient’s relative. The appropriate measures are used to guarantee maximum data confidentiality. All patient-related clinical data will be anonymized locally. 

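### Consent before entry, with a relative route stated only for death in the ICU, leaves some in-hospital deaths and incapacitated survivors with no stated way into the registry, so in-hospital mortality may be biased, probably downward

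*Protocol article*

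**What the plan says.** Section 2.5 sets the target population: "The KOS-ACS Registry will enroll all patients admitted, at any of the registered clinical centers", with a diagnosis of ACS.

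Section 2.9 sets the conditions of entry:

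- Consent comes first: "All patients must give informed consent before entering their personal and clinical data in the KOS-ACS Registry".
- One time point is given: "Patients will give informed consent after transfer from an intensive care unit (ICU) to a cardiac/coronary care unit".
- One substitute is given: "In the case of death in the ICU, consent to use the patient’s data anonymously will be given by a patient’s relative".

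Section 2.6 makes early death an outcome: "In-hospital death and complications will be registered". The third objective in section 2.1 concerns associations of ACS characteristics with "clinical outcomes, including mortality, complications, the length of hospital stay, and the quality of clinical care".

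Section 2.7 describes the quality check. Every three months, registry experts "will check the validity of entered data by reconciling randomly selected records with the data of patients’ hospital charts".

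**The concern.** The entry rules and the population statement do not fit together. If the rules in section 2.9 are followed as written, entry depends on surviving and being able to sign, or on dying in the one place for which a relative's consent is provided. Survival to discharge is itself an outcome of the registry, so this is selection related to the outcome.

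The discussion section wants the registry to measure Kosovan care against guidelines and against other nations. A mortality figure taken from an incompletely captured population would weaken those comparisons. It could also blur comparisons between centers if the uncaptured share differs among them. The article says that service is not uniform nationally, but it gives nothing on how capture might vary.

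The quarterly check would not reveal the problem. It starts from records already entered, so it cannot find patients who never were.

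**Working it through.** The article states no mortality rate, no capture rate and no sample size, so there is no planned figure to reproduce. The check has two parts.

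**1. Who has a stated route under section 2.9**

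| Admitted patient | Stated route |
|---|---|
| Leaves the ICU for a cardiac or coronary care unit and can consent | Own consent |
| Dies in the ICU, relative consents | Relative, anonymous data |
| Dies in the ICU, no available or willing relative | None stated |
| Dies in hospital outside the ICU before consenting | None stated |
| Survives but lacks capacity | None stated |

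The last three rows conflict with enrolling every admitted patient. The third and fourth rows remove deaths; the fifth removes survivors. They push the recorded mortality in opposite directions.

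**2. Direction and size, on assumed inputs**

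Let

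- m = true in-hospital mortality;
- f = share of in-hospital deaths that occur in the ICU;
- r = share of ICU deaths captured through a relative;
- q = share of other in-hospital deaths captured;
- c_d = f·r + (1 − f)·q, the share of all deaths captured;
- c_s = share of survivors captured.

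Recorded mortality = m·c_d / [m·c_d + (1 − m)·c_s].

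Equivalently, recorded odds of death = true odds × c_d/c_s. Mortality is understated if c_d < c_s, unbiased if they are equal, and overstated if c_d > c_s.

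All values below are assumptions, with q = 0 (no death outside the ICU is captured).

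| m | f | r | c_d | c_s = 100% | c_s = 90% | c_s = 80% |
|---|---|---|---|---|---|---|
| 5% | 0.80 | 1.0 | 0.80 | 4.04% | 4.47% | 5.00% |
| 5% | 0.80 | 0.8 | 0.64 | 3.26% | 3.61% | 4.04% |
| 5% | 0.95 | 1.0 | 0.95 | 4.76% | 5.26% | 5.88% |
| 8% | 0.80 | 1.0 | 0.80 | 6.50% | 7.17% | 8.00% |
| 8% | 0.80 | 0.8 | 0.64 | 5.27% | 5.82% | 6.50% |
| 8% | 0.95 | 1.0 | 0.95 | 7.63% | 8.41% | 9.36% |

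Worked example, second row, c_s = 100%: 0.05 × 0.64 / (0.05 × 0.64 + 0.95 × 1) = 0.032 / 0.982 = 3.26%.

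A wider grid (f of 0.6, 0.8 and 0.95; r of 1.0, 0.8 and 0.5; q of 0 and 0.5; c_s as above) gives recorded values from 1.55% to 6.03% for a true 5%, and from 2.54% to 9.58% for a true 8%. Most combinations understate, some show no bias, and a few overstate. The grid was chosen for illustration, so these counts are not probabilities.

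**The case against.** The strongest reply is that this is a condensed article. Section 2.9 refers to a study protocol and consent forms approved by two ethics bodies, and section 2.7 to a user manual still to be written. Any of these may cover incapacity, absent relatives or deaths outside the ICU. The article does not say that its consent routes are exhaustive, and it does not say when patients who never enter an ICU consent. This stands as a limit on certainty. It does not remove the point, because the article states a rule for all patients and a single exception, and a reader cannot infer others.

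Several stronger readings are tempting, but the document does not support them:

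- *The sickest patients drop out.* ICU deaths are foreseen and have a route through a relative, so the gap is narrower than that.
- *In-hospital mortality is understated.* This needs deaths to be captured less often than survivors. Assuming that 5% of survivors and 20% to 50% of deaths are lost turns a true 7% into 6.0% to 3.8%, but those inputs fix the sign in advance.
- *Transferred patients are lost.* Sections 2.4 and 2.5 place all invited Kosovan centers in the registry, so a patient moved within Kosovo stays among participating hospitals. Nothing bars consent at the receiving one.
- *Deaths in the emergency room contradict complete enrollment.* Section 2.5 concerns admitted patients. Those who die before admission are outside the stated population.
- *This is immortal-time bias, and every association with early death is distorted.* No exposure or follow-up time is misclassified; this is selection related to the outcome. If capture depended only on whether the patient died, odds ratios for predictors of death would be preserved, as in case-control sampling. They are distorted only if capture depends jointly on the predictor and on death.

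**Conclusion.** The point holds in limited form. As written, section 2.9 gives no route for in-hospital deaths outside the ICU before consent, for ICU deaths without a consenting relative, or for survivors lacking capacity. The enrollment stated in section 2.5 is therefore not assured, and the mortality that the registry sets out to measure may be biased.

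Downward bias is the likelier direction, since two of the three uncovered groups are deaths. Neither sign nor size follows from the document: both rest on the ratio of capture among deaths to capture among survivors, which it does not give. On the assumed inputs tabulated above, a true 5% is recorded as anything from 3.26% to 5.88%.

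This is a cheap improvement rather than a fatal defect. It is best made early, because analysis cannot recover patients of whom no trace was kept.

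**What to change.** 1. In section 2.9, extend the relative's consent to anonymous data use from ICU deaths to any in-hospital death before consent, subject to ethics approval. If the full protocol already covers this, say so in one sentence.
2. Keep a short anonymous log at each center of every eligible admission not entered: age band, sex, ACS type, vital status at discharge, and reason. This also counts ICU deaths without a consenting relative and survivors lacking capacity.
3. Report capture separately for deaths and survivors, overall and by center. Give in-hospital mortality both for entered patients and with logged patients added to the denominator and logged deaths to the numerator.

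The cost is an ethics amendment, which should also cover the log, and a small amount of extra data entry for the coordinators. Collecting fuller data without consent from living patients who lack capacity is a separate ethics question. It is not needed for this fix, because the log is enough to measure the gap.

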## 3. Discussion

National medical registries have become a well-established practice in many countries and among different academic organizations. The main benefit of medical registries is the transparent and detailed documentation of a patient’s medical condition, risk factors, clinical presentation, management pathway, and clinical outcome. Such an approach allows for an accurate evaluation of the national management strategies and potential deviation from international guidelines. It also allows for risk factors’ comparison and clinical outcome between different countries in and away from the same geographical region. The first published registry on myocardial infarction was from Warsaw emergency service in 1979 [33], followed by many registries from different countries, worldwide. The most recently published is the national Moroccan registry of ST-elevation MI [34]. Kosovo is a small-sized country, recently established with steadily developing infrastructure and economy. Likewise, medical services have been developing in different specialties including cardiovascular disease. Primary coronary intervention has now nationally matured with a clinical outcome comparable to other countries in the region [32,35,36]. The optimum control and prevention of coronary artery disease and ischemic heart disease in Kosovo, however, remain a challenge since the clinical service provided is not nationally uniform but depends on individual center expertise and facilities. In addition, the coronary disease prevention strategy in Kosovo has not matured yet. The Kosovo Society of Cardiology, established in 2002, has already made a plausible scientific and academic success with many cardiologists obtaining higher degrees from international universities and returning to support the local clinical services and bring international knowledge into daily practice for their patients. Despite this, there is a lack of a formal structured documentation system in the form of a registry which should assist clinicians and scientists to study, in detail, the nature of national Kosovo coronary artery disease, in terms of the pattern of presentation, contributing risk factors, and management pathways. Also, such a registry should help in conducting an accurate comparison of the latter information with respective ones from other nations, in light of the international available guidelines’ recommendations. Once achieved, the results should assist in drawing an accurate clinical road map for managing coronary artery disease in Kosovo.

The Kosovo Society of Cardiology has agreed to establish a national registry for coronary artery disease, the summary of which is described in this report, and the results of its analysis should assist in achieving the registry objective, in particular the evaluation of coronary disease services against published clinical guidelines and comparing its details with respective ones from other nations.

## Figures and Tables

**Figure 1 diagnostics-14-01486-f001:**
[figure not shown]
Objective, inclusion and exclusion criteria of the study patients.

**Figure 2 diagnostics-14-01486-f002:**
[figure not shown]
The development plan of the registry.

**Figure 3 diagnostics-14-01486-f003:**
[figure not shown]
The follow-up plan of the registry.

## Data Availability

The data underlying this article will be shared on reasonable request to the corresponding author.
